### Data collecting and monitoring

Data monitoring will be conducted by the Science and Technology Department of Acupuncture &Tuina Institute, SHUTCM. Clinical test data will be captured through case report forms (CRFs) by paper questionnaires or by online data capture applications and store in a secured location. Confidentiality will be maintained through the assignment of an encrypted number code. Data entry was double-checked for accuracy. The test data will be locked and analyzed by two statisticians under the supervision of a third statistician and the administrators. Then, the test data will be recorded on the sub-website of China Clinical Trial Center (http://www.medresman.org.cn/login.aspx) electronic data management system. The electronic database will be closed after data entry is completed. The administrators are required to report weekly data monitoring progress to the Steering Committee regularly, including the accuracy and reliability of data.

Trial auditing involves periodic independent review of core trial processes and documents, such as data monitoring and scheduling monitoring. Data monitoring will be conducted by the Science and Technology Department of Acupuncture &Tuina Institute, SHUTCM. The monitors will verify that all adverse events were documented in the correct format and are consistent with protocol definition. The monitor will verify the following variables for all patients: initials, date of birth, sex, signed informed consent, eligibility criteria, date of randomization, treatment assignment, adverse events, and endpoints. Scheduling monitoring visits will be a function of COVID-19 patient enrollment, site status, and other commitments. The investigators must be available to meet with the monitors. If a problem is identified during the visit (i.e., inadequate or insufficient staff to conduct the study, missing study documents), the monitor will assist the site in resolving the issues. The focus of the visit/electronic monitoring will be on source document review and confirmation of adverse events.

### Statistical analysis

#### General analysis principles

The statistical analysis plan of this trial refers to the previous published study protocol [25, 27]. In the case of continuous variables, Lilliefors corrected Kolmogorov–Smirnov tests will be applied to assess the normality. Continuous variables will be presented as descriptive statistics (mean ± the standard deviation (SD) for data with normal distribution or median (interquartile range) for nonnormally distributed data). Categorical data will be calculated with frequency counts and percentages of participants. Tests of statistical significance will be conducted at the two-tailed *α* level of 0.05. Statistical analysis will be performed in IBM SPSS version 28 (IBM Corp., Armonk, NY, USA).

#### Analysis of primary outcome

The primary outcomes will be evaluated at baseline, 12 weeks after the intervention, and follow-up. We will conduct sensitivity analyses for missing data (intention-to-treat analysis) and for adjustment of covariates of physical activity (adjusted intention-to-treat analysis). The primary endpoint is the mean change in mMRC Scales from baseline to the follow-up day. Baseline covariates included are sex, age category, history of cardiopulmonary disease, and body weight category. The whole outcomes scale will be measured at baseline. When normally distributed, the data will be analyzed with unpaired *t*-test for comparison between two groups, while for multiple comparisons one-way ANOVA and repeated measures (RM) ANOVA will be used. A sensitivity analysis using multiple imputation techniques (imputation using chained equations) will be included to assess the effect of missing data on the primary outcome. Besides, we will compare participants randomly allocated to BT group or KQG group, who received an allocated treatment that was deemed to be of high fidelity. The percentage of missing data is 20% and 5 imputed datasets will be used for analysis, which is the minimum recommended number. Prior to any analysis, any missing data pattern will be investigated and the reasons for missing data will be obtained and patterns will be investigated to judge the plausibility of missingness assumptions.

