### Exclusion criteria

Any involvement in the following condition will be removed: (1) patients with complications of underlying noncommunicable diseases such as chronic obstructive pulmonary disease, coronary heart disease, dementia, chronic kidney disease, immunosuppression, and cancer; (2) patients with mental illness; (3) patients with cognitive dysfunction until unable to understand the whole trial process; (4) patients with severe bone or joint diseases that affect movement (e.g., spinal arthritis, severe osteoporosis, and periarthritis); (5) patients with pregnancy or lactating; (6) cigarettes smokers; (7) patients who participate in other form of exercise programs during trial.

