### Primary outcome measurements

#### Modified Medical Research Council (mMRC) Dyspnea Scale

The mMRC Dyspnea Scale will be used as the primary outcome indicator to evaluate the dyspnea symptoms and physical health; mMRC score is a good indicator of the functional capacity of patients’ lungs [30]. The mMRC grades [31] are as follows: mMRC grade 0, dyspnea occurs only during strenuous exercise; mMRC grade 1—the patient has shortness of breath when walking on flat ground or walking on a small slope; mMRC grade 2—due to shortness of breath, when walking on flat ground, the patient is slower than another person of the same age or needs to stop to rest; mMRC grade 3—when walking on flat ground for approximately 100 m or after a few minutes, the patient needs to stop to pant; and mMRC grade 4—due to severe breathing difficulties, the patient cannot leave the house or has breathing difficulties when dressing or undressing. The mMRC score will be assessed with a repeated longitudinal analysis.

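### The primary t-test on mMRC change leaves baseline mMRC out of the covariates; adjusting for it would gain precision at no data cost

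*Protocol article*

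**What the plan says.** All of the following is in the protocol article; no separate SAP is at hand.

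- **Endpoint** (Analysis of primary outcome): "The primary endpoint is the mean change in mMRC Scales from baseline to the follow-up day".
- **Two-group test** (same section): "When normally distributed, the data will be analyzed with unpaired" t-test. No covariate is attached to it.
- **Other tests** (same section): "for multiple comparisons one-way ANOVA and repeated measures (RM) ANOVA will be used".
- **Covariates** (same section): "Baseline covariates included are sex, age category, history of cardiopulmonary disease, and body weight category". The text does not say which model uses them.
- **Baseline data** (same section): "The whole outcomes scale will be measured at baseline". Baseline mMRC will therefore be available.
- **Adjusted analysis** (same section): a sensitivity analysis "for adjustment of covariates of physical activity (adjusted intention-to-treat analysis"). Physical activity is not on the baseline covariate list, and the time at which it is measured is not given.
- **Outcome description** (mMRC section): "The mMRC score will be assessed with a repeated longitudinal analysis".
- **Eligibility** (Exclusion criteria, item 1): excluded are "patients with complications of underlying noncommunicable diseases such as chronic obstructive pulmonary disease, coronary heart disease" and others.

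**The concern.** In a trial with a repeated outcome scale, the baseline value of that scale is usually the best single predictor of the later value. Here it is collected from everyone, yet the covariate list passes over it in favour of sex, age, weight and disease history. Subtracting baseline does use it, but with a slope forced to 1. When the true slope is below 1, subtraction over-corrects: an arm that starts worse by chance tends to show more improvement.

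With 30 per arm, such chance differences are not small. At stake are the width of the confidence interval for the primary effect and the power for effects smaller than planned. The validity of the test is not at stake.

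Two smaller points belong with this one. A listed covariate overlaps with an exclusion criterion. And the physical-activity adjustment is not tied to baseline, in a trial whose arms are exercise programmes.

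**Working it through.** **Inputs from the protocol**

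- Sample size calculation: SDs 0.55 and 0.54, so the pooled SD is √((0.55² + 0.54²)/2) = 0.545; means 0.74 and 1.52, so the difference is 0.78; loss to follow-up 20%.
- Study design and Fig. 1: 60 in total, 30 per arm, so 30 × 0.8 = 24 evaluable per arm.

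**Assumptions**

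- The baseline-to-follow-up correlation (rho) is not in the document; 0.3, 0.5 and 0.7 are shown.
- SDs are equal at both visits, and 0.545 is the SD of the raw score.
- mMRC has five ordered grades, so the variance formulas are approximate.

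**The plan's own figure.** The protocol gives no precision figure for this comparison. Its sample size inputs (difference 0.78, SD 0.545, two-sided 5%) give 9 per group at 80% power by t-test, or 12 after 20% dropout; at 90% power they give 12, or 15 after dropout. Neither 60 nor 30 per group is reproduced. Nothing below depends on that, and the variance ratio is the same at any sample size.

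**Precision**

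- Change score, variance per participant: 2·SD²·(1 − rho).
- ANCOVA on baseline: SD²·(1 − rho²).
- Ratio: (1 − rho²) / [2(1 − rho)] = (1 + rho)/2, which is below 1 for every rho below 1.

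Power is two-sided 5%, noncentral t, with 24 per arm:

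| rho | Variance ratio | SE, change | SE, ANCOVA | Difference with 80% power, change | ANCOVA power at that difference | Power at 0.40 (illustrative), change → ANCOVA | Power at 0.78, change → ANCOVA |
|---|---|---|---|---|---|---|---|
| 0.3 | 0.65 | 0.186 | 0.150 | 0.533 | 93% | 56% → 74% | 98.4% → 99.9% |
| 0.5 | 0.75 | 0.157 | 0.136 | 0.450 | 90% | 70% → 82% | 99.8% → over 99.9% |
| 0.7 | 0.85 | 0.122 | 0.112 | 0.349 | 86% | 89% → 94% | over 99.9% for both |

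For equal power, the ANCOVA needs 35%, 25% or 15% fewer participants.

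**Chance imbalance.** The SE of the baseline difference with 30 per arm is 0.545 × √(2/30) = 0.141, so 95% of trials fall within about ±0.28 points (1.96 × 0.141). Given a baseline difference b, the expected change-score contrast moves by −(1 − rho)·b. At b = 0.28 that is about 0.20, 0.14 or 0.08 points for rho 0.3, 0.5 or 0.7. An ANCOVA removes this shift.

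**RM ANOVA.** The contrast of group by time from baseline to follow-up is the same as the change-score test. A group main effect over all three visits would average (0 + d + d)/3 = 2d/3, but averaging also lowers the variance. Under compound symmetry and a constant effect, the squared signal-to-noise ratio, in units of d²/SD², is:

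| rho | Main effect, 4/[3(1 + 2rho)] | Change, 1/[2(1 − rho)] | ANCOVA, 1/(1 − rho²) |
|---|---|---|---|
| 0.3 | 0.83 | 0.71 | 1.10 |
| 0.5 | 0.67 | 1.00 | 1.33 |
| 0.7 | 0.56 | 1.67 | 1.96 |

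**The case against.** The best defence is that nothing here is an error. Under randomisation, the t-test on change is unbiased and already uses baseline mMRC. At the protocol's own difference, both methods have ample power. The correlation is assumed. The article is condensed and refers its analysis plan to earlier published protocols, so the model's detail may sit elsewhere. All of this limits the size of the point. It does not remove it, because the article states a test and a covariate list, and that list omits the baseline outcome.

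A further caution stands. In the sample size section the treatment mean exceeds the control mean on a scale where higher is worse. The figures may therefore be improvements, and 0.545 a change-score SD. The ratio (1 + rho)/2 would survive, but the detectable differences would change. The imbalance SE would become 0.12, 0.14 or 0.18, from a raw SD of 0.545/√(2(1 − rho)).

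A reader might infer three stronger claims that the text does not support:

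- *RM ANOVA dilutes the primary effect to two thirds.* The protocol gives the two-group comparison to the t-test and never makes a group main effect the primary test. At rho 0.3 that main effect would even be the stronger test (0.83 against 0.71).
- *The plan adjusts for a disease it excludes.* The overlap is partial. Item 1 concerns complications of such diseases, so past or uncomplicated disease, or other heart and lung conditions, could still enter. No figure shows the covariate to be constant.
- *The physical-activity adjustment removes part of the treatment effect.* That follows only if activity is measured after randomisation, which is not stated, and the analysis is a sensitivity analysis.

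**Conclusion.** The point holds as a free improvement. The stated primary comparison is valid, but it is less precise than one adjusted for baseline mMRC, and it stays exposed to chance imbalance at baseline.

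The variance ratio of 0.65 to 0.85 rests on an assumed rho of 0.3 to 0.7 and equal SDs; its direction holds for any rho below 1. The absolute figures also rest on 0.545 being the raw-score SD and on 24 evaluable participants per arm.

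It would be wrong to conclude that the plan is biased, or underpowered for the difference it assumes: at 0.78, power is about 98% or more with either method. The benefit lies in interval width and in power for smaller effects, which are plausible because the comparator is itself an active breathing programme. The cardiopulmonary-history and physical-activity items need clarifying; neither is shown to be an error.

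**What to change.** 1. Make the primary analysis an ANCOVA of follow-up mMRC on group and baseline mMRC, or a longitudinal mixed model of the post-baseline visits with baseline mMRC as a covariate. Report the group difference with its confidence interval at the named follow-up visit.
2. If RM ANOVA is kept, base the treatment test on the group-by-time contrast, not on a group main effect that includes the baseline visit.
3. Reconcile the cardiopulmonary-history covariate with exclusion criterion 1. Drop or redefine it if few participants with such a history can enter.
4. Limit any physical-activity adjustment to values recorded at baseline.

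The cost is wording only. For the main change (items 1 and 2), baseline mMRC is already scheduled, no visit or participant is added, and the SPSS package named in the protocol fits these models. The change should be fixed before the database is locked and the analysts are unblinded.

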#### Analysis of secondary outcome

Analysis of secondary outcome will be undertaken referring to analysis of primary outcome. We will test for between arm differences for each endpoint specified. Chi-square test or Fisher’s exact test will be adopted to analyze the adverse events (AEs).

### Quality control

The study will be overseen by a steering committee during the whole processing of the trial. All the researchers will be trained with the trial methodology and monitoring technique before participating in the trial. Participants will be remotely monitored online and supervised offline by coordinators.

### Safety evaluation

Safety evaluations will be conducted at screening, throughout the trial, and at follow-up 12 weeks after the last TCMRE, although TCMRE programs are low risk. Any adverse events (AEs) will be collated from CRFs and follow-up questionnaires. Even though BT and KQG are at low risk. AEs will be collated from CRFs and follow-up questionnaires. Researchers will then analyze whether AEs are directly related to the rehabilitation program. When sports injuries occur or condition suddenly deteriorates during the trial with serious complications or severe adverse effects such as breathing difficulties, severe anxiety, severe depression, the trial will be terminated immediately and prompt medical treatment will be administered according to the condition of the subject. Researchers will then analyze whether they are directly related to the rehabilitation program.

## Discussion

In March 2022, a large-scale outbreak of coronavirus disease occurred again in Shanghai, China. As the number of discharged patients increased, the sequelae of discharged patients gradually became the focus of clinical attention [2]. Despite the relatively low overall mortality rate as compared to the previous COVID-19, yet fatigue, depression, or cognitive impairment (brain fog) symptoms encountered by discharged patients also need immediate and appropriate rehabilitation treatment. The prevalence of sleep problems during the COVID-19 pandemic is approximately 40% of people from the general and health care populations [42]. The Chinese government has taken instant medical measures and rescue efforts to control further deterioration of the pandemic. These measures include intensive surveillance, epidemiological surveillance, symptomatic supportive treatment, and active application of Traditional Chinese medicine (TCM), for the purpose of reducing mortality and shortening hospital stay [25, 40]. All medical expenses for COVID-19 disease treatment are fully subsidized by the China Health Insurance; however, the convalescence treatment of discharged patients is still a huge medical burden. Therefore, it is necessary to find more non-drug therapies to cope with the sequelae of this pneumonia.

Taiji [43, 44], Yijinjing Qigong [45], Shaolin Neigong [46], Wuqinxi Qigong [47], Liuzijue Qigong[48], and Baduanjin Qigong [49, 50] belong to the category of supplementary medicine and alternative medicine and are widely used in disease prevention, treatment, and rehabilitation [40, 51, 52]. Some researchers [52–55] have attested that Taiji, Yijinjing Qigong, Shaolin Neigong, Wuqinxi Qigong, Liuzijue Qigong, and Baduanjin Qigong can improve the clinical symptoms, along with physical and mental health of patients with lung diseases. TCMRE projects are highly operational and cost-effective due to overburdened healthcare system [56, 57]. Studies found that exercise may be beneficial for improving pulmonary symptoms and suppressing inflammation in discharged patients [49]. KQG exercise prescription adopted in this study consists of seven exercises: Starting form and warm-up, Liu Zi Hu Xi Xuan Fei Qi, Kai He Kuo Xiong He Qi Xue, Guan Jing Tui La Zeng Qi Li, Tai Chi Fei Tiao Yin Yang, Ti Zhong Dun Zu Xiao Bai Bin and losing form. KQG is a low-risk therapy that combines the advantages of Taiji, Yijinjing Qigong, Shaolin Neigong, Wuqinxi Qigong, Liuzijue Qigong, and Baduanjin Qigong, with neither need for heavy equipment nor constrained by time or location [17]. KQG is more targeted to the cardiopulmonary function, fatigue state, and emotional disturbance of COVID-19 patients. By combining literature research and the actual application of KQG exercise in Wuhan Leishenshan Hospital and Huangshi Hospital of Traditional Chinese Medicine, KQG is considered eligible to participate in the rehabilitation treatment of discharged COVID-19 patients [17, 25]. KQG will promote recovery for the majority of patients and improves the living quality of patients [17, 25]. The human immune system is able to counteract the damage of foreign microorganisms through dynamic regulation of innate immunity by TCMRE [40, 57], and increasing muscle strength and respiratory muscle endurance to relieve dyspnea, anxieties, and tension associated with negative situations [25]. TCMRE is capable of coordinating Qi and blood, adjusting the balance of Yin and Yang from the macro theory of TCM. Nonetheless, stronger evidence is needed to further demonstrate the effectiveness of KQG exercise prescription in improving clinical symptoms of COVID-19 discharged patients. Thus, this clinical trial will further evaluate the rehabilitation effect of KQG on discharged patients.

## Study limitations

An inevitable limitation of this study is that BT intervention and KQG intervention cannot blind participants and therapists. The outcomes may be affected because patients can know their group and anticipate the treatment effect in advance.

## Trial status

This trial will recruit patients on May 2022 and is expected to end in December 2022. This protocol is v.10 (the 1st version) dated April 2022.

## Data Availability

The protocol manuscript does not contain any data, so we declare that data and materials are not applicable in this study. However, the datasets generated and analyzed during the study will be available in the [Figshare] repository when the trial is complete.

## Abbreviations

COVID-19: 2019 Novel coronavirus
TCMRE: Traditional Chinese medicine rehabilitation exercises
KQG: Kangyi Qiangshen Gong exercise prescription
BT: Breathing techniques according to WHO
RCT: Randomized controlled trial
SPIRIT: The Standard Protocol Items: Recommendations for Interventional Trials
LF: The principal investigators
WC: Study coordinator
mMRC: Modified Medical Research Council
PSQI: Pittsburgh Sleep Quality Index
